## Outcome measures

Baseline assessment will occur as close as possible to the MDT treatment decision. All patients repeat assessments immediately prior to surgery. Patients undergoing neoadjuvant cancer treatment (e.g. chemoradiotherapy for locally advanced rectal cancer patients) will undergo repeat CPET every 4-weeks (depending on site availability), in order to assess continued eligibility and to moderate training intensities according to physiological adaptation. Post-operative assessment occurs during hospital admission, at 30 days post-surgery, at 6- and 12- weeks post-surgery and 12-months post-surgery. The schedule of observations and procedures can be found in the
*Extended data*.
^
62
^

## Primary outcome

Length of stay is defined as the number of days a patient stays in hospital following surgery. It is calculated by subtracting the date of surgery from the date of discharge. The date of surgery is defined as day 0 of a patient’s post-operative hospital stay.

## Secondary outcomes

i.World Health Organisation Disability Adjusted Survival 2.0 (WHODAS 2.0) - The 36 item WHODAS 2.0 questionnaire will be completed at baseline, prior to surgery, day-30, week-12 and 12-months following date of surgery.ii.Post-operative morbidity will be determined by the post-operative morbidity survey (POMS),
^
54
^ the highest in-hospital morbidity achieved according to the Clavien-Dindo-Demartines (CD) score
^
45
^ and the comprehensive complication index (CCI) score.
^
46
^ Patients’ POMS will be characterised on day 3, 5, 7 and 15, while patient remains hospitalised. The POMS 18-item survey will be used to address nine domains of postoperative morbidity (pulmonary, infectious, renal, gastrointestinal, cardiovascular, neurological, wound complication, haematological and pain). On day of discharge, patient’s surgical complications (if any) will be graded using the CD classification of surgical complications This classification is used to assess overall hospital morbidity following surgical procedures. Patients are graded as 0 (no complications) or Grade I-V based on the level of complication, including the number of organ system involvement. Grade V is defined as death of a patient. A record of the CCI – an update of the CD classification will also be collected.iii.Health related QoL will be assessed using the EQ-5D-5L
^
46
^ and the EORTC-QLQ-C30.
^
47
^ EQ-5D-5L is a standardised measure of health status which provides a simple, generic measure of health for clinical and economic appraisal. There are 5 domains (mobility, self-care, usual activities, pain/discomfort, anxiety/depression) each with 5 levels of health. It also includes a visual analogue scale which asks the respondent to rate their health from 0 (worst imaginable) to 100 (best imaginable health). Cancer specific, health-related QoL will be measured using the EORTC-QLQ-C30. This EORTC-QLQ-C30 measures physical, role, emotional, social and cognitive functioning, as well as global QoL and three symptoms; fatigue, pain and nausea/vomiting. For all scales scores range from 0-100. For global and functional scales higher scores reflect favorable QoL, whereas higher symptom scales score indicate more symptoms.

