### Secondary outcomes

i.WHODAS total score, and each category score (cognition, mobility, self-care, interpersonal relationships, life activities and participation in society) will be summarised by intervention group at baseline, 30 days, 12 weeks and 12 months using mean (standard deviation) or median (interquartile range) depending on the normality of data.ii.Disability free survival will be assessed by identifying whether the patient has a WHODAS score less than 25% at 1-year post surgery, and will be compared between treatment groups using logistic regression. A multivariate analysis may be performed adjusting for clinically prognostic factors, as specified for the primary endpoint.iii.The Clavien-Dindo complication score is an ordinal variable with classification grades I, II, IIIa, IIIb, IVa, IVb, V. The wilcoxon-mann-whitney test will be used to compare between groups. If appropriate, ordinal logistic regression will be used to perform an analysis adjusted for important prognostic variables. The CCI score provides a measure of overall morbidity over the whole period following an intervention, which is reflected on a scale from 0 (no complication) to 100 (death). Data will be checked for Normality and summarised using mean (SD) or median (IQR) as appropriate. If the scores are normally distributed, a t-test will be used to compare groups, and linear regression modelling may be considered in order to adjust for baseline characteristics. For non-normal data, we will check whether logistic transformation improves normality. If not, the wilcoxon-mann-whitney test will be used. The proportion of patients with post-operative morbidity according to POMS will be summarised in each of the nine domains by intervention group/day. Due to the repeated nature of the data, mixed modelling will also be considered.iv.The EQ 5D subscales and overall Health scale will be tabulated at each timepoint (baseline, pre-surgery, week-12 and 12-months post-surgery). Linear mixed modelling will be performed with overall health scale as the outcome variable, and intervention group and baseline health scale as explanatory variables to investigate the effect of intervention considering all timepoints. This will be repeated for the EORTC-QLQ-C30 global health score, and mixed effects ordered logistic regression will be considered for analysis of subscales.

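### Clavien-Dindo is closed at discharge and POMS is taken only in inpatients, so both morbidity measures depend on length of stay, the primary outcome, and their comparisons could be distorted

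*Protocol article*

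**What the plan says.** All references are to the protocol article.

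- **CD.** Secondary outcomes, item ii, defines the measure as "the highest in-hospital morbidity achieved according to the Clavien-Dindo-Demartines (CD) score" and sets the time of grading: "On day of discharge, patient’s surgical complications (if any) will be graded using the CD classification of surgical complications".
- **CCI.** The same item says only that this index, "an update of the CD classification will also be collected"; it gives no window or later time point. Statistical analysis plan, Secondary outcomes, item iii, says: "The CCI score provides a measure of overall morbidity over the whole period following an intervention".
- **POMS collection.** "POMS will be characterised on day 3, 5, 7 and 15, while patient remains hospitalised".
- **POMS analysis.** "The proportion of patients with post-operative morbidity according to POMS will be summarised in each of the nine domains by intervention group/day". Then: "Due to the repeated nature of the data, mixed modelling will also be considered". Neither sentence says how a patient already discharged on a given day is handled.
- **Comparisons.** CD is compared between groups by the Wilcoxon-Mann-Whitney test, with ordinal logistic regression if appropriate. CCI is compared by a t-test or the Wilcoxon-Mann-Whitney test. Neither allows for length of observation.
- **Primary outcome.** Length of stay runs from surgery to discharge. The trial is designed to shorten it by 1 day from a control median of 7 (Estimation of sample size).
- **Other visits.** Outcome measures lists a post-operative assessment at 30 days. The article assigns no complication grading to it.

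**The concern.** The date of discharge ends the primary outcome. It also closes the CD window and decides who has a POMS record on days 3, 5, 7 and 15. If the intervention shortens stay, which is the trial's hypothesis, the arms are no longer observed alike.

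The two effects run in opposite directions. An earlier discharge leaves less time for a complication to be counted under CD, which favours the intervention. For POMS, well patients leave first. A comparison restricted to those still in hospital then sets a smaller, sicker remnant of the intervention arm against a larger remnant of the control arm. This can make the intervention look worse or hide a benefit. The morbidity measures could therefore disagree with each other, or with the truth, in just the case where the trial succeeds on its primary outcome.

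**Working it through.** **Inputs from the article:** control median stay 7 days; hazard ratio (HR) for discharge 1.17; 1560 patients randomised 1:1:1:1 and analysed on two factorial margins; 20% drop-out; POMS on days 3, 5, 7 and 15. Per margin: 1560/2 = 780, and 780 × 0.8 = 624.

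**Assumptions:** exponential stay in steps 1 to 3; those in steps 4 and 5 are stated there. The article gives no POMS prevalence and no distribution of complication onset.

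**Step 1: the plan's own effect.** With exponential stay, the intervention median is 7/1.17 = 5.98 days. This agrees with the stated 1-day reduction.

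**Step 2: who is still in hospital.** Control S0(t) = 0.5^(t/7); intervention S1(t) = S0(t)^1.17.

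| Day | Control | Intervention | Patients of 624 v 624 |
|---|---|---|---|
| 3 | 74.3% | 70.6% | 464 v 441 |
| 5 | 61.0% | 56.0% | 380 v 350 |
| 7 | 50.0% | 44.4% | 312 v 277 |
| 15 | 22.6% | 17.6% | 141 v 110 |

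**Step 3: POMS on day 7 with an inpatient denominator and no treatment effect on morbidity.** Let m be the share of all operated patients with POMS morbidity, all of them still in hospital. The inpatient proportion is m/S.

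- m = 20%: 0.20/0.500 = 40.0% v 0.20/0.444 = 45.0%, a spurious excess of 5.0 points.
- m = 30%: 0.30/0.500 = 60.0% v 0.30/0.444 = 67.5%, a spurious excess of 7.5 points.

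With all operated patients as denominator, the difference is 0 in both cases.

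A simulation gives larger gaps. Recovery time is lognormal with median 4.5 days and log-SD 0.5, 0.7 or 0.9, and only the wait from recovery to discharge is shortened so that median stay falls from 7 to 6 days. Day-7 inpatient prevalence is then 37.4% v 51.0%, 52.7% v 66.6% and 62.3% v 74.8%, a gap of 12.5 to 13.9 points. This is an extreme case, because the whole gain in stay comes from that wait, and it is not carried into the conclusion.

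**Step 4: POMS when the intervention does reduce morbidity.** Suppose day-7 morbidity falls in proportion to the inpatient share: 30% × 44.4/50.0 = 26.7%. The inpatient proportions are then 60.0% v 60.0%, and a real difference of 3.3 points disappears. In the same simulation with recovery and stay both multiplied by 6/7:

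| Log-SD | All operated, day 7 | Inpatients only, day 7 |
|---|---|---|
| 0.5 | 18.7% v 11.5% (7.2 points) | 37.4% v 30.8% (6.6) |
| 0.7 | 26.4% v 19.7% (6.7) | 52.7% v 49.7% (3.0) |
| 0.9 | 31.1% v 25.4% (5.7) | 62.3% v 61.5% (0.8) |

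The benefit is diluted by an amount that depends on the spread of recovery times.

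**Step 5: CD counted to discharge with no treatment effect on complications.** Assumptions: 50% of patients in each arm have a complication by day 30; onset is exponential with scale 4, 7 or 14 days, truncated at day 30, and independent of discharge; stay is lognormal with median 7 v 6 days and log-SD 0.5 or 0.7.

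| Onset scale | Log-SD 0.5 | Log-SD 0.7 |
|---|---|---|
| 4 days | 40.2% v 38.0% | 39.3% v 37.2% |
| 7 days | 32.0% v 29.4% | 31.8% v 29.5% |
| 14 days | 23.2% v 20.7% | 23.8% v 21.4% |

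Before rounding, the spurious gain for the intervention is 2.0 to 2.6 points. With 624 per side, a two-sided 5% test of any complication would reject in 11% to 18% of trials. The plan tests grades by Wilcoxon, so these rejection rates are only a guide. Counted over a fixed 30 days, the rates are 50% v 50%.

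**The case against.** **The POMS analysis is not fixed in the article.** A reader might infer that POMS will be analysed in inpatients only, or that discharged patients will be treated as missing at random. The article says neither. It states no denominator and commits to no between-group POMS test, and its proportion of patients by group and day can be read as covering all operated patients. The discharge date is collected, and a SAP not shown may settle the coding. This stands: the POMS part is conditional on the denominator.

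**CCI closure at discharge is an inference.** The in-hospital wording attaches to CD, and the phrase about the whole period can be a general description of the instrument. A reader might call this a contradiction, but the text does not go that far. What remains is a missing window and two descriptions that need to be reconciled.

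**In-hospital morbidity is intended.** The Conclusion section names in-hospital complications. That is a legitimate outcome, and a 30-day grade is a different one. But intent does not make the window independent of treatment, and the secondary objective is worded as post-operative morbidity in general.

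**The schedule in the extended data is not shown** and might add a 30-day complication record. If so, it should be reconciled with the CD definition in the article.

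**The CD effect is small.** A window 1 day in 7 (14%) shorter does not mean 14% fewer complications, and a complication that itself delays discharge is counted in either arm. This stands and limits the CD part to a modest bias.

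**Conclusion.** The concern holds as a dependence on length of stay that could distort the morbidity comparisons.

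- **CD:** fixed by the text. If stay is shortened, the comparison could be biased in favour of the intervention by about 2 to 3 points, given a 50% 30-day complication rate and onset independent of discharge.
- **CCI:** its window needs to be stated and reconciled with the description in the analysis section.
- **POMS:** conditional on an inpatient denominator. With 50.0% v 44.4% in hospital on day 7, a spurious excess of 5.0 to 7.5 points arises if day-7 morbidity is an equal 20% to 30% of all operated patients. If the intervention does reduce morbidity, the likelier result is a masked benefit.

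A reader might infer that both morbidity results would simply be artefacts of length of stay. The documents do not support that. With equal stay and equal discharge practice there is no distortion, and a real effect on morbidity would contribute to any difference seen.

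**What to change.** **CD and CCI.** Grade both over a fixed 30 days from surgery at the 30-day assessment already scheduled, and include complications at readmission. Keep the in-hospital grade as a supporting summary. State the CCI window once and use it in both the outcome and the analysis sections. The cost is a small amount of extra data entry; some post-discharge events may be under-recorded.

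**POMS.** State that the denominator on each day is all operated patients. Count patients discharged alive before that day as free of POMS morbidity, and deaths as morbidity. Fit any repeated-measures model to these completed data. State the assumption openly, because it fails for anyone who leaves with morbidity or develops it after leaving. No new data are needed; the cost is wording.

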## Exploratory outcomes

i.Overall and disease-free survival at 1-year post-surgeryii.VO
_2_ at AT (anaerobic threshold), VO
_2_ at peak, and VE-VCO
_2_ slope. Other CPET variables will be reported and analysed as per previous publications.
^
8,
12,
35,
44
^
iii.Radiological makers of body composition will be measured from routine abdominal computed tomography (CT) scans at L3.
^
54,
55
^
iv.Radiological tumour downsizing/sizing/regression will be assessed using CT, magnetic resonance imaging (MRI) and positron emission tomography (PET) scans for all patients including those who have received neoadjuvant treatments. Clinical radiological tumor, node and metastasis (TNM) and tumour specific regression scores (RECIST
^
56
^) will be recorded after each clinical scan (baseline and re-staging).v.Body composition will be measured using bioelectrical impedance analysis at baseline, immediately before surgery and at 6- and 12-weeks after surgery using the supplied SECA
^TM^ body composition analyser MBCA 515 weighing scale.vi.Patients will undertake assessments through the trial in order to characterise nutritional status and relate to post-operative outcome, response to the trial interventions and response to neoadjuvant cancer treatments.vii.Objective physical activity levels will be determined in a sub-sample of participants by ActiGraph
^TM^ GT9X link activity sensor, worn for 5 complete days, following baseline CPET, +/-during cancer therapies and at 12-weeks and 12-months following surgery.viii.Quality-adjusted life years (QALY) will be used as a measure of health outcome for economic evaluation, incorporating both the quantity and the quality of patients’ lives. The EQ-5D-5L will be used to evaluate QALYs to evaluate both the morbidity gains and the mortality impact of prehabilitation in cancer patients.
^
57
^
ix.Anxiety and depression will be measured using the hospital anxiety and depression scale (HADS).
^
58
^
x.Self-efficacy (confidence) to self-manage chronic disease (SEMCD), will be measured using the Lorig SEMCD scale.
^
59
^
xi.Patient activation will be measured using the PAM (patient activation measure).
^
60
^

## Process evaluation

Qualitative in-depth semi-structured interviews will be conducted with patients enrolled in the trial and professionals involved in the delivery of the trial at two time points. Interviews of up to 1 hour will be conducted either face to face at a location convenient to the participant or by telephone depending on preference. A researcher with experience in qualitative interviewing and who is not part of intervention delivery will conduct the interviews. Firstly, patients from all arms of the study (N = 12) and key stakeholders; personal trainers, research nurses and counsellors (N = 5) will be interviewed regarding their experiences of the trial once the first 30 patients have reached 12 weeks post-surgery. The sample size is pragmatic based on the time and resource available early in the trial and will provide an opportunity for the research team to reflect on the experiences of patients and professionals involved in the trial, identifying barriers and facilitators to trial processes and implementation (professionals) and trial experiences (patients). If any amendments to the trial are deemed necessary, a substantial amendment will be submitted to the ethics committee and Health Research Authority (HRA) for approval.

Following completion of the trial structured interviews will be conducted with 25 patients (with representation from all 4 study arms) to understand patient experience of the trial and subsequent behaviour change. The sample size is will allow for purposive sampling with sampling characteristics including a range of age, sex, disease type, and whether or not they received neoadjuvant treatments. Interviews will also be conducted with stakeholders involved in the delivery of the trial, to include personal trainers, counsellors, research nurses (including other research team members) and members of clinical care teams, commissioners and cancer centre staff (N = 15). These interviews will seek to understand the barriers and facilitators to the implementation of the trial into clinical practice and within the community setting. All interviews will be audio-recorded, transcribed verbatim managed through
NVIVO software (v12) and analysed using thematic analysis with an inductive approach. Normalisation process theory will inform data collection and analysis.
^
61
^

## Estimation of sample size

From previous studies, the median length of stay in the control group is estimated to be 7 days. To detect a clinically meaningful difference of a (significance level to detect a hazard ratio of 1.17 when the control group median in-patient time is 7 days) 1 day reduction in LOS with 85% power, alpha = 0.05, a sample size of 1560 participants will need to be recruited over 3 years, with a one year follow-up period. The sample size allows for a 20% drop-out.

Sample size calculations for 2×2 designs are based on the two main comparisons (i.e. exercise vs. no exercise and psychological support vs. no support). The trial sample size is the larger of these 2 comparisons, so in this case, the sample size calculation is powered on the psychological support comparison. The sample size calculation assumes that there is no interaction between the interventions.

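### At a two-sided alpha of 0.05, 1560 patients with 20% lost to the primary analysis give about 79% power for HR 1.17, not the stated 85%

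*Protocol article*

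**What the plan says.** All the design figures are in the protocol article, section Estimation of sample size.

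- Control group: "the median length of stay in the control group is estimated to be 7 days".
- Effect: a one-day reduction, given as a "significance level to detect a hazard ratio of 1.17 when the control group median in-patient time is 7 days".
- Error rates and size: "1 day reduction in LOS with 85% power, alpha = 0.05, a sample size of 1560 participants will need to be recruited".
- Attrition: "The sample size allows for a 20% drop-out".
- Comparison: the two factorial main effects, assuming no interaction.

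The section Recruitment and randomisation gives equal allocation to four groups, so each main effect compares 780 with 780. The Primary outcome part of the Statistical analysis plan section models time to discharge by competing-risks regression, with in-hospital death as the competing event. It also expects some randomised patients never to have surgery. The article gives no sidedness for alpha, no event count and no in-hospital death rate.

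**The concern.** Hazard ratio, power, alpha, total number and drop-out are all printed, so the statement can be checked without the full protocol. Under the usual two-sided reading the number falls short of what 85% power needs once the stated drop-out is removed. In that case the type II error for the primary outcome is about 21% rather than 15%. A reader of a null result who relies on the printed power would then take it as stronger evidence against a one-day benefit than the design supports. Neither type I error nor bias is affected.

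**Working it through.** **Inputs.** HR 1.17, alpha 0.05, power 85%, N = 1560 and drop-out 20% come from Estimation of sample size; the 1:1 margins come from Recruitment and randomisation. Two assumptions are mine: alpha is two-sided unless I say otherwise, and every patient who remains is discharged alive. The second favours the plan.

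**Effect size.** Under exponential stays, a fall in the median from 7 to 6 days is HR 7/6 = 1.1667, which rounds to the stated 1.17. Conversely 7/1.17 = 5.98 days. The effect size is consistent with itself, and I carry both values.

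**Events needed for 85% power** (Schoenfeld, 1:1): D = 4 (z_alpha + z_power)² / (ln HR)², with z_power = 1.036.

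| Alpha | HR | Events | Randomised, events/0.8 |
|---|---|---|---|
| Two-sided, z = 1.960 | 1.17 | 4 × 2.996² / 0.1570² = 1457 | 1822 |
| Two-sided | 7/6 | 1512 | 1890 |
| One-sided, z = 1.645 | 1.17 | 1167 | 1459 |
| One-sided | 7/6 | 1211 | 1514 |

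Freedman's formula gives nearly the same totals: 1829 and 1898 two-sided, 1465 and 1519 one-sided.

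**Can 1560 be reproduced?** No variant returns it exactly. Two come within 3%, both at HR 7/6:

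- One-sided 0.05 with the 20% removed gives 1514 to 1519.
- Two-sided 0.05 with drop-out entered only as censoring at 20% per year gives 1521 to 1527. Such censoring hardly touches a seven-day stay.

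Two-sided 0.05 with the 20% removed does not come close.

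**Power of the plan as stated.** Power = Φ(√(D/4) × ln HR − z_alpha), with D = 1560 × 0.8 = 1248. For HR 1.17, √312 × 0.1570 = 2.773, so two-sided power is Φ(2.773 − 1.960) = Φ(0.813) = 79.2%.

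| Events | Two-sided, HR 1.17 | Two-sided, HR 7/6 | One-sided, HR 1.17 | One-sided, HR 7/6 |
|---|---|---|---|---|
| 1248 (20% lost) | 79.2% | 77.7% | 87.0% | 85.9% |
| 1300 (1560/1.2) | 80.8% | 79.4% | 88.2% | 87.2% |
| 1560 (none lost) | 87.3% | 86.1% | 92.7% | 91.9% |

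**Loss the design can bear.** Two-sided 85% at HR 1.17 allows 1 − 1457/1560 = 6.6% lost before discharge. At HR 7/6 it allows 1 − 1512/1560 = 3.1%.

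**Effect detectable with 1248 events.** exp(2 × 2.996/√1248) = 1.185, a median of 7/1.185 = 5.9 days.

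**In-hospital death.** The article gives no rate. If 0 to 5% of the 1248 die before discharge (assumed range), two-sided power at HR 1.17 falls from 79.2% to 77.1%.

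**The case against.** The strongest reply is that sidedness is not stated. With a one-sided 0.05 test and the full 20% lost, power is 85.9% to 87.0%, so the stated figure is met. That stands. A reader might infer that the plan simply fails to deliver 85% power, or that recruitment must rise to 1822. The article does not support either conclusion without the two-sided condition. The one-sided reading is nevertheless unstated and unconventional for a phase III trial, and it comes near 1560 only if the printed HR of 1.17 is replaced by 7/6.

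The second reply concerns where drop-out occurs. The allowance is mentioned next to the one-year follow-up, and length of stay is complete at discharge. The section Data collection, quality and storage keeps data collected before withdrawal unless consent for their use is withdrawn. Patients lost between discharge and 12 months would therefore still count, and if all 1560 did, two-sided power would be 86.1% to 87.3%. This is possible in part, because the article does not split the 20%. It is weak as a full answer: the allowance is attached to the sample size for the primary outcome, length of stay starts at surgery, and the analysis section expects randomised patients who never reach surgery. Such patients have no post-operative stay to analyse.

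A reader might also infer that 1560 came from an 80% power calculation, since that gives 1592 (dividing by 0.8) or 1529 (multiplying by 1.2). Neither equals 1560, and other variants come about as near, so the origin of the number is not established.

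Finally, an article may leave the formula and event count to the full protocol. That is fair, and their absence is not the point. The point is that the printed figures disagree under their conventional reading.

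**Conclusion.** The point holds conditionally. If alpha is two-sided 0.05 and the stated 20% is lost to the primary analysis, the 85% power and the drop-out allowance cannot both be true with 1560 patients. Power is then about 79% for HR 1.17 and 78% for HR 7/6, a shortfall of 6 to 7 percentage points. It is about 81% for HR 1.17 if 1560 was obtained as 1300 × 1.2. These values rest on 1:1 margins, no interaction and no in-hospital deaths; any deaths lower them slightly. The 85% survives in only two ways: a one-sided 0.05 test, or losses before discharge of no more than about 6.6% (3.1% at HR 7/6). The article states neither, so the sentence needs correcting or qualifying on every reading.

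**What to change.** Keep 1560 patients, state that alpha is two-sided, and restate the power, for example: *with 20% drop-out (1248 evaluable), each main-effect comparison has about 79% power to detect HR 1.17 at two-sided alpha 0.05 (85% power for HR 1.185).*

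If the calculation was in fact one-sided, or assumed that most drop-out occurs after discharge, say so explicitly and give the two-sided power at 1248 evaluable next to it.

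The cost is a change of wording in one section and, on the two-sided reading, a less favourable stated power. It needs no extra patients and no change to the analysis.
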